### Additional outcomes

The following clinical outcomes will be collected retrospectively for all three phases: Blood creatinine, BUN level, acute and chronic rejection, infection, health-related quality of life and death from the medical record and from primary data collection. Acute and chronic rejection episodes will include those that are biopsy-proven and/or medically treated (3-day dose of intravenous prednisone) as such. Infection episodes will include those in which the blood, sputum, and/or urine culture is positive for an abnormal organism. Deaths will be reported from the transplant team.

### Cost-effectiveness

The primary endpoint of cost-effectiveness measures will be the incremental cost-effectiveness ratio (ICER) of the SystemCHANGE™ intervention relative to the attention-control, which assesses the incremental cost per health-related quality-adjusted life year gained. The perspective of cost-effectiveness is a third-party payer. A micro-costing approach will be used to measure the intervention’s resource use, based on a log of resource use for each intervention. The resources used for the delivery intervention in the interventional and the control group will be tracked over the study period. The Pps will track the type and quantity of medical services consumed (doctor’s office, clinic, hospital, medication). The unit cost of personnel time will be based on actual hourly salary rates and fringe benefits. Unit costs of each hospitalization, ER visit, clinic visit, and physician fee will be estimated based on Medicare’s average reimbursement rate. The unit cost of medication will be estimated from the average wholesale price plus the dispensation fee of 2 %. To determine the number of quality-adjusted life years over the observational period, the weight will be multiplied by the number of days in the observational period. All cost measures will be adjusted to the constant U.S. dollar. Sensitivity analyses will examine key parameters that may affect ICERs.

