## Design

This is a 4-year, two-center, randomized controlled trial, that is single-blind (participants [Pps]) and uses a stratified sample block design with repeated measures. We are comparing the SystemCHANGE™ intervention to the attention control intervention in adult kidney transplant recipients with existing medication nonadherence documented by electronic monitoring. The repeated-measures design provides longitudinal data regarding medication nonadherence which allows us to determine when the intervention becomes effective (to determine if a lower dose of SystemCHANGE™, e.g. shorter time of delivery, is possible). It also allows us to track possible decay in medication nonadherence over time following the intervention.

We are examining the experimental effect on the outcome variable MA. During the 3-month screening phase, all Pps are using electronic monitoring to document medication taking. Those who are adherent (MA rate of .85 % or greater) exit the study. To prevent the “ceiling” effect, those with documented medication nonadherence (MA rate of less than .85 %) are stratified by low (<70 %), and moderate (70-84 %) nonadherence, based upon our previous medication nonadherence pattern research [41]. They then enter the intervention phase of the study and are randomized into either the treatment (SystemCHANGE™ intervention) or the attention control group (attention control condition). During the 6-month intervention phase, all Pps receive a home visit at baseline plus six telephone calls (at intervention months 1, 2, 3, 4, 5, 6). In addition, Pps randomized into the SystemCHANGE™ intervention are also guided in implementing SystemCHANGE™ activities related to medication taking by the Research Assistant (RA). Control group Pps receive RA-provided education guided by healthy living patient educational materials. The maintenance phase begins after the intervention and runs for an additional 6 months. This phase examines how Pps maintain MA in the absence of an intervention; however, we are continuing to use electronic monitoring to measure the outcome variable. Health outcome and healthcare cost data are collected during the intervention and maintenance phases.

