### Attention-Control intervention

The 6-month attention-control intervention involves a home visit and monthly phone calls at the same intervals as the intervention group (at attention-control months 1, 2, 3, 4, 5, and 6). Rather than the SystemCHANGE™ intervention, the attention-control Pps receive educational materials developed by the International Transplant Nurses Society that address healthy living after transplant [50]. The RA calls Pps at 1, 2, 3, 4, 5 and 6 months to review the brochure information and answer any questions about it. Time, interval, frequency, and setting are all exactly the same for the intervention and control groups. If attention-control Pps raise questions about medications or medication-taking, the RA directs them to discuss them with their transplant team contact person.

At the end of month 6 of the intervention phase, the RA closes the control by discussing the healthy post-transplant information the Pp reviewed during the previous 6 months. The RA encourages Pps to continue using the electronic medication monitor and diary for the next 6 months during maintenance phase.

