Our third exploratory aim is to determine if the SystemCHANGE™ intervention is cost-effective. Our hypothesis is the cost for the SystemCHANGE™ intervention will be less than the cost for the attention-control intervention. To determine the cost-effectiveness of the SystemCHANGE™ intervention compared to the attention-control intervention, both intervention and resource use costs will be evaluated and compared to MA change. A cost-effectiveness analysis will be performed at the end of the intervention period and again at the end of the maintenance period. If there is no treatment effect, a cost-analysis will not be performed. The analysis performed at the end of the maintenance period will be cumulative, incorporating costs and benefits incurred throughout the project. A cost-effectiveness analysis, performed at the end of the maintenance period (calculated for both the intervention and maintenance periods), will evaluate both intervention and control, and resource use costs which will be compared to adherence change. The sum of the total intervention and control costs and resource use costs will be the numerators for testing this hypothesis. The change in adherence (from baseline to end of intervention [or end of maintenance] period) will be the denominator. We will identify all direct intervention costs related to the intervention and the control (planning, designing, and implementation of each intervention, personnel, supplies, travel, and equipment). We will identify resource use costs (hospitalizations, clinic, observation, and ER visits) for both groups. Resource use costs will be obtained from publically available data, e.g. Hospital Compare, Hospital Stats, H-CUP. The DRG will be obtained with a conversion rate and then adjusted by hospital specific information, e.g. academic, location.

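### The payer-perspective ICER nets out the delivery cost of a contact-matched attention control, so it does not show what a payer adopting SystemCHANGE would spend on delivery and monitoring

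*Protocol article*

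**What the plan says.** The Cost-effectiveness section names as its primary endpoint the "incremental cost-effectiveness ratio (ICER) of the SystemCHANGE™ intervention relative to the attention-control", expressed as cost per quality-adjusted life year. It adds that "The perspective of cost-effectiveness is a third-party payer" and that "The resources used for the delivery intervention in the interventional and the control group will be tracked over the study period". It promises sensitivity analyses on key parameters without naming them.

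The third exploratory aim under Statistical analysis says "We will identify all direct intervention costs related to the intervention and the control", covering items such as planning, staff, supplies, travel and equipment. It then describes a cost-to-adherence ratio: "The sum of the total intervention and control costs and resource use costs will be the numerators for testing this hypothesis", with change in adherence as the denominator. The Aims section likewise hypothesises a lower cost-effectiveness ratio for SystemCHANGE than for the control.

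On contact, the Design section says "all Pps receive a home visit at baseline plus six telephone calls (at intervention months 1, 2, 3, 4, 5, 6"), and the Attention-Control section says "Time, interval, frequency, and setting are all exactly the same for the intervention and control groups". The control consists of educational brochures on healthy living, reviewed with a research assistant.

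On monitoring, Design puts every participant on electronic monitoring for the three-month screening phase. The section on the primary outcome keeps both arms on the caps afterwards, but only SystemCHANGE participants are sent the reports, because feedback is a step of that intervention.

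**The concern.** An attention control is built to match contact, so that a difference in adherence can be attributed to the content of SystemCHANGE. That suits the primary aim. A payer has a different question: what will it cost to add this programme to existing care? For that, the relevant delivery cost is the whole of SystemCHANGE, not its excess over a matched control. The article describes that control as a study condition and never as care a payer would otherwise fund.

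Because the ICER is defined against this control, and delivery is costed in both arms, most of the programme's own cost drops out. The caps needed for feedback, and the monitoring needed to find eligible patients, add nothing to the increment either. At stake is a payer-perspective result that leaves out most of the cost of adoption, in an article whose Discussion foresees clinicians delivering the intervention at reasonable cost.

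**Working it through.** The documents give no cost or ICER figure, so there is none to reproduce. The check splits the ICER numerator into its parts.

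Numerator = (D_S − D_C) + (M_S − M_C) + (H_S − H_C), where D is delivery cost, M monitoring cost, H health-care resource cost, S is SystemCHANGE and C is attention control.

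**Delivery, D.** Inputs from the article:
- SystemCHANGE home visit of about 1 h 20 min = 80 min (Development of the SystemCHANGE intervention)
- six monthly calls in both arms (Design)
- same time, interval, frequency and setting in both arms (Attention-Control intervention)
- a SystemCHANGE call two weeks after the home visit, not described for the control (Development section)

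Call length is not stated. I assume c = 10 to 45 min, and take the control visit as 80 min because time is said to be the same.

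- Control contact time = 80 + 6c
- SystemCHANGE = 80 + 6c, or 80 + 7c if the two-week call is extra
- Increment = 0, or c

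| c (min) | SystemCHANGE, six calls | Increment | SystemCHANGE, seven calls | Increment | Share of gross |
|---|---|---|---|---|---|
| 10 | 140 | 0 | 150 | 10 | 6.7% |
| 20 | 200 | 0 | 220 | 20 | 9.1% |
| 30 | 260 | 0 | 290 | 30 | 10.3% |
| 45 | 350 | 0 | 395 | 45 | 11.4% |

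The ICER thus retains 0% to about 11% of gross contact time. Travel to the home visit is not in the table. With the same setting in both arms it would cancel too, and counting it would lower the share.

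**Monitoring, M.** Both arms use the caps for the six intervention months, so that increment is 0. Screening comes before randomisation, and those found adherent leave the study and enter neither arm's costs, so screening contributes 0 as well.

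For scale, 190 are screened (Abstract) and the final sample is 92 (Statistical analysis): 190/92 = 2.07. Then 2.07 × 3 months = 6.2 screening monitor-months, and 6.2 + 6 = 12.2 monitor-months per patient in the final SystemCHANGE sample, against a net increment of 0. The 92 is the final sample and the number randomised is not given. If more than 92 are randomised, 2.07 overstates the number screened per randomised patient.

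**Health care, H.** Hospital, clinic, observation and emergency costs enter for both arms and can differ. Nothing cancels here by design.

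**The other ratio.** The Aims and the third exploratory aim read as one cost-to-adherence ratio per arm. In such ratios nothing is subtracted and the full delivery cost stays. But they are not incremental and do not use quality-adjusted life years, so they do not supply what the Cost-effectiveness section defines as its primary endpoint.

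**The case against.** The article names its comparator openly, and the as-trialled ICER is internally consistent: costs and effects both come from the same randomised contrast. A no-programme comparator asks a further question. Replacing the control's delivery cost with zero while keeping its outcomes pairs a no-programme cost with an effect measured against attention, and that pairing is valid only under an added assumption. The Discussion also foresees delivery in hospital or clinic, so the gross trial cost need not equal a payer's cost, and part of the screening serves to avoid a ceiling effect in the trial. All of this stands. It is why the as-trialled ICER should stay and the payer calculation should be a scenario beside it.

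A reader might go further and infer that SystemCHANGE is made to look almost free, or that almost any adherence gain would appear cost-effective. The documents do not support that. The ICER in the Cost-effectiveness section divides by quality-adjusted life years, so an adherence gain alone does not enter it. The ratios that do divide by adherence change appear to be per arm, and there the costs do not cancel. Worksheets, expert training, mailed reports and possibly one extra call can differ between arms, as can health-care use. That no payer funds the control is likewise an inference from how it is described, not a statement in the article.

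It can also be said that naming scenarios belongs in a fuller plan. But comparator, perspective and cost components are all fixed in this article, and the point concerns how they combine. An unspecified sensitivity analysis on parameters does not promise another comparator.

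**Conclusion.** The point holds for the ICER in the Cost-effectiveness section. Its delivery component is small by design: 0% to about 11% of gross contact time, the upper end applying only if the two-week call is additional, and apart from differences in materials, training and reports. Cap and screening costs also cancel. This rests on the stated matching of contacts, the assumed call lengths of 10 to 45 minutes and a control visit of equal length. The ICER as defined answers how SystemCHANGE compares with an equally intensive control. It does not show what a payer would spend to adopt the programme, and conclusions about payer cost-effectiveness should not rest on it alone.

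The consequence is limited. The aim is exploratory, the cost analysis is done only if there is a treatment effect, and the adherence comparison is unaffected.

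**What to change.** Keep the as-trialled ICER against the attention control. Add to the Cost-effectiveness section a prespecified payer-perspective scenario, reported beside it, that:

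- sets the attention-control delivery cost to zero and keeps that arm's health-care costs
- charges SystemCHANGE its full delivery cost and the caps and reports used for feedback
- shows, as a further variant, the screening cost per patient actually randomised, using the observed numbers screened and randomised

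State the scenario's assumption beside the result: that the attention control changes neither outcomes nor resource use relative to usual care.

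Reconcile the per-arm cost-to-adherence ratios in the Aims and the third exploratory aim with the cost-per-QALY ICER. Also reconcile the two-week SystemCHANGE call with the statement that contact is identical in both arms.

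The cost is small. Delivery resources are already to be logged for each intervention, so little is needed beyond recording cap and screening costs. The downside is a less favourable ratio that depends on the stated assumption.

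### The QALY rule multiplies the weight by days without converting to years; applied literally it yields quality-adjusted days and a cost per QALY about 365 times too small

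*Protocol article*

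**What the plan says.** The Cost-effectiveness section of the protocol article names the ICER of SystemCHANGE relative to attention control as the primary cost-effectiveness endpoint, "which assesses the incremental cost per health-related quality-adjusted life year gained". Later in the same paragraph it gives the derivation: "To determine the number of quality-adjusted life years over the observational period, the weight will be multiplied by the number of days in the observational" [...].

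The weight is not defined further. The Additional outcomes section lists what is collected across the three phases, including "acute and chronic rejection, infection, health-related quality of life and death from the medical record and from primary data collection", but names no quality-of-life instrument or scale.

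The period can be inferred from two places. The Statistical analysis section says that "A cost-effectiveness analysis will be performed at the end of the intervention period and again at the end of the maintenance period", the second analysis being cumulative. The Design section says that "The maintenance phase begins after the intervention and runs for an additional 6 months". The two horizons are therefore about 6 and 12 months.

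The Statistical analysis section is the only other account of the economic analysis. It does not use QALYs: "The change in adherence (from baseline to end of intervention [or end of maintenance] period) will be the denominator".

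**The concern.** The endpoint is expressed per life year, while the derivation is expressed in days. The sentence labels its result as life years, but the operation it prescribes gives quality-adjusted days. This is not a detail left to a fuller document: the article states a formula, and the formula does not give the quantity it names.

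What is at stake is the absolute size of the cost per QALY. That number is normally set beside a value threshold or beside other studies. A figure per quality-adjusted day reported as a figure per QALY would mislead any such comparison.

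**Working it through.** The article reports no QALY or ICER figure, so there is nothing to reproduce. The check is one of units.

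**Inputs**
- Endpoint unit: cost per QALY, that is, per year (Cost-effectiveness).
- Rule: weight × days (Cost-effectiveness).
- Horizons: 6 months, taken as 182.625 days, and 12 months cumulative, taken as 365.25 days (Design; Statistical analysis).
- Assumption: the weight *w* is on the usual scale where 1 is full health. The article does not give the scale.

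**Formulas**
- Rule as written: Q_lit = w × days.
- QALY: Q = w × days / 365.25.
- Hence Q_lit / Q = 365.25.
- With ICER = ΔC / ΔQ, the correct ICER divided by the literal one is also 365.25. ΔC, Δw and the number of days all cancel.

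**QALYs per patient**

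| Horizon | w | Rule as written | QALY |
|---|---|---|---|
| 6 months | 0.80 | 0.80 × 182.625 = 146.1 | 0.40 |
| 6 months | 1.00 | 182.625 | 0.50 |
| 12 months | 0.80 | 0.80 × 365.25 = 292.2 | 0.80 |
| 12 months | 1.00 | 365.25 | 1.00 |

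**ICER, illustration only.** The cost and weight differences below are assumed; the article gives neither.
- ΔC = $500, Δw = 0.02, 12 months: the literal rule gives 500 / (0.02 × 365.25) = $68.45. In years it is 500 / 0.02 = $25,000 per QALY.
- ΔC = $1,000, Δw = 0.02, 12 months: $136.89 against $50,000.
- ΔC from $200 to $5,000, Δw from 0.01 to 0.05, 6 or 12 months: $10.95 to $2,737.85 by the literal rule, against $4,000 to $1,000,000 per QALY.

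The dollar values depend on the assumptions. The factor of 365.25 does not.

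**Search for a conversion.** Neither the Cost-effectiveness section nor the Statistical analysis section divides by the days in a year or gives another QALY rule. The adherence denominator in the Statistical analysis section does not repair the rule, because it is a different quantity. Which denominator the trial intends is a separate question; choosing QALYs would still leave this sentence wrong.

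**The case against.** The strongest reply is that this is loose wording. The paragraph names the life year both in the endpoint and in the rule itself. A total of 292 QALYs for one patient followed for one year is impossible on its face, and an experienced analyst would supply the division. That stands as a reason to expect that the error would be caught, so it cannot be said that the trial will report a wrong ICER. It does not make the sentence correct, and no other rule in the article could replace it.

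The second reply concerns consequence, and it largely stands. The economic aim is exploratory, and the Statistical analysis section drops the cost analysis if there is no treatment effect. The Aims section hypothesises a lower cost-effectiveness ratio in the intervention group than in the control group; a factor common to both arms cancels there. The hypothesis of lower cost in the Statistical analysis section involves no QALY.

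Some stronger readings are tempting, but the article does not support them:
- A reader might infer that almost any cost would be declared cost-effective. The article sets no willingness-to-pay threshold, so no such decision rule can be shown to fail.
- A reader might infer from the singular noun that one weight is applied to the whole period, so that a gain fading between 6 and 12 months is missed. The article does not say how often the weight is measured or how values are combined, and it lists quality of life as collected in all three phases. An article may leave such detail to the full protocol.
- A reader might infer that days after death are credited. That requires the observation period to be a fixed 12 months for everyone, which the text does not say.
- A reader might take the missing quality-of-life row in Table 2 as further evidence. It has no bearing on the unit error.

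**Conclusion.** Wrong as written, minor severity. The one stated rule gives quality-adjusted days under the name of QALYs. Applied literally, it inflates QALYs and shrinks the absolute ICER by a factor of 365.25, with the sign unchanged. This rests on the weight being on the usual scale with 1 as full health, and on no conversion being made elsewhere in documents not shown. The effect is confined to the reported size of the cost per QALY in an exploratory aim; the adherence comparisons are not affected.

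**What to change.** In the Cost-effectiveness section, have the rule multiply the weight by the days in the observation period divided by 365.25, or equivalently by the length of that period in years. This is a change of one phrase. It needs no new data, visits or questionnaires and alters no other analysis. The unit error calls for nothing more.

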### Potential moderators and mediators

Perceived health status, a potential moderator, will be measured by one question, “In general, how would you say your health is?” Respondents select excellent, very good, good, fair, or poor. Perceived health status reflects people’s overall perception of their health, including both physical and psychological dimensions [58]. The question has good reliability and validity [58]. Ethnicity will also be examined as a moderator.

Potential mediators are examined including social support and systems-thinking. We measure social support using the Social Support Appraisals Index, a 23-item self-administered, self-report scale measuring the degree to which a person feels cared for, respected, and involved with family and friends [59]. Respondents strongly agree, agree, disagree, or strongly disagree with each statement. Total scores range from 23 to 92. After reversing the negatively stated items, low scores indicate high levels of support. Typically, subscale scores for family and friends are calculated. The instrument has been used with adult kidney transplant recipients [43, 60]. Data from 10 samples indicate that the scale had good internal reliability, with Cronbach’s alphas ranging from .80 to .90 [59]. The scale also showed stability over a six-week interval, with reliability scores of .80. Convergent validity has been demonstrated with significant associations to seven other appraisal measures. Moreover, adequate concurrent, and divergent validity with other perceived support measures was demonstrated.

Personal Systems Thinking will be measured by Systems Thinking Survey (adapted for patients), a 20-item scale using a 5-point Likert response scale developed by [name]. The scale measures perceptions of personal system behaviors [61]. It has good reliability and construct and discriminate validity [62]. Test-retest was 0.74 and Cronbach’s Alpha was 0.89 [62]. The tool discriminated between those receiving high and low or no SystemCHANGE training (*p*=.05 and .01, respectively).

